#### Sample size

The sample size for this study was determined using G-Power software, considering various aspects of genital self-image. Referring to the research conducted by Weitkamp et al. [18], with values M1 = 29.09, M2 = 24.11 (assuming a 20% increase due to the intervention's impact), SD1 = SD2 = 3.22, a two-sided α of 0.05, and a Power of 90%, the sample size for each group was initially computed as 15. The final sample size for each group was established at 17 individuals to accommodate a potential 10% dropout rate.

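### The printed sample-size inputs give about 10 women per group, not 15, so the inputs, the 90% power and the n cannot all be right

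*Protocol article*

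**What the plan says.** The Sample size section under Phase III is the only justification given for the trial's size. It names the program ("The sample size for this study was determined using G-Power software") and says that aspects of genital self-image were considered. It takes its values from a cited study, "with values M1 = 29.09, M2 = 24.11 (assuming a 20% increase due to the intervention's impact", with an SD of 3.22 in both groups. It then reports "a two-sided α of 0.05, and a Power of 90%, the sample size for each group was initially computed as 15", and finally "The final sample size for each group was established at 17 individuals to accommodate a potential 10% dropout rate".

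The section does not name the test behind the calculation. The Analysis approach section lists independent t-tests, analysis of covariance and Mann–Whitney tests among the methods. Neither section mentions a reduced alpha, a multiplicity split or a design factor.

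Two other sections bear on the point. The Phase III data collection section gives the genital self-image scale (FGSIS) a range of 7 to 28. The outcome sections make intention to undergo surgery, or its actual performance, the primary outcome and list the FGSIS as secondary.

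**The concern.** The section prints everything needed to repeat a two-group comparison of means: both means, the SD, alpha, sidedness, power and one n for both groups. A difference of about one and a half standard deviations is very large, and 15 per group is visibly more than it needs at 90% power.

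If the figures do not fit together, a reader cannot tell what effect the trial was sized to detect. The apparent margin may be genuine. Or it may vanish, if the calculation was in fact run with a smaller difference or a larger SD than the ones printed.

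**Working it through.** **Inputs, all from the Sample size section.** M1 = 29.09, M2 = 24.11, SD = 3.22 in each group, two-sided alpha 0.05, power 90%, equal groups, stated n = 15 per group, dropout 10%, final n = 17 per group.

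**Effect size.** Difference = 29.09 − 24.11 = 4.98. Standardised difference d = 4.98/3.22 = 1.547.

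**Attempt to reproduce 15.**
- Normal approximation: n = 2(1.960 + 1.282)²/1.547² = 21.0/2.39 ≈ 8.8, so 9 per group.
- Exact noncentral t for two independent means: n = 9.85, so 10 per group.

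The figure 15 is not reproduced.

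**Power for the printed inputs (exact t, two-sided 0.05).**

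| n per group | Power |
|---|---|
| 9 | 86.8% |
| 10 | 90.5% |
| 14 | 97.6% |
| 15 | 98.3% |
| 17 | 99.2% |

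**Could another reading of the same inputs give 15?**

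| Variant | n per group |
|---|---|
| One-sided alpha 0.05 | 8 |
| Paired t-test | 7 |
| Mann–Whitney, relative efficiency 0.955 (9.85/0.955 = 10.3) | 11 |
| Mann–Whitney, minimum efficiency 0.864 (9.85/0.864 = 11.4) | 12 |
| Exact 20% increase (0.20 × 24.11 = 4.82 points) | 11 |
| 95% power | 12 |

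A simulation of the Mann–Whitney test with normal data agrees: power is 87.5% at 10 per group, 91.5% at 11 and 97.6% at 15.

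**What would give 15?** Only inputs that the section does not state, changing one at a time under the t-test:
- power of 98% (14 per group falls short at 97.6%, and 15 gives 98.3%);
- two-sided alpha of 0.01 at 90% power (14.2, rounded up to 15);
- an SD near 4.06 (at n = 15 and 90% power the detectable d is 1.226, and 4.98/1.226 = 4.06);
- a difference near 3.95 (1.226 × 3.22 = 3.95).

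**Dropout step.** 15/(1 − 0.10) = 16.7, so 17. This reproduces, so the break lies in the 15 or in what fed it.

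**What the planned size delivers for genital self-image.** 17 × 0.9 = 15.3, so take 15 analysed per group, with SD 3.22, a t-test and two-sided alpha 0.05.
- 80% power: d = 1.06, and 1.06 × 3.22 = 3.41 points.
- 90% power: d = 1.226, and 1.226 × 3.22 = 3.95 points.

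The room above 24.11 on a scale ending at 28 is 28 − 24.11 = 3.89 points, so the 90% figure reaches the ceiling (24.11 + 3.95 = 28.06).

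**The case against.** The strongest reply is that the error is harmless. For the printed effect, 15 per group gives 98.3% power and 17 gives 99.2%, so the trial is larger than its own inputs require. That stands. This mismatch does not by itself leave the trial underpowered for that effect.

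A second reply is that the test is not named and that several aspects of self-image were considered. The 15 might then be the largest n across those aspects, printed beside the inputs of one of them, or the 15 might itself be the misprint. That also stands, as a reason not to say which figure is wrong. It does not remove the mismatch, because the section presents the 15 as the result of these inputs. The figure of 10 depends on the t-test, but Mann–Whitney at 11 to 12 does not close the gap.

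A reader might go further and infer that the design effect is unattainable, since 29.09 lies above the FGSIS maximum and a difference of 3.95 from 24.11 gives 28.06. The documents do not support this as a conclusion about the true design assumption. The section does not say that the two means are FGSIS scores, although the FGSIS is this trial's instrument and the reading is plausible. The value 28.06 arises only if 24.11 and the SD of 3.22 are both right and the difference alone is wrong, which is one of several ways to reach 15. An assumption that cannot be identified cannot also be declared infeasible.

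**Conclusion.** The point holds as a mismatch between printed figures. The inputs give 10 per group by the t-test, or about 11 to 12 by Mann–Whitney, against a stated 15. Measured against 15, power is about 98%, not 90%. The inputs, the power and the n cannot all be right, and nothing in the article shows which is wrong. The result assumes two independent groups of equal size compared once at the stated alpha.

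Two further readings are not supported. One is that 10 is the right size for the trial: that would treat the printed inputs as correct, which is exactly what is in doubt. The other is that 17 per group is vindicated because it exceeds 10: the calculation concerns genital self-image, a secondary outcome, and says nothing about the size needed for surgery intention or performance.

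**What to change.** Re-run the calculation with the inputs actually intended. If the FGSIS is the scale meant, use a mean that can occur on 7 to 28. Name the test, and print inputs, power and n that reproduce one another.

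With planned enrolment unchanged, add a sentence on what the size delivers for genital self-image: with SD 3.22 and 15 analysed per group, a detectable difference of about 3.4 points at 80% power and 3.9 at 90%. State beside it that 3.9 points above 24.11 reaches the top of the scale, and that the calculation concerns a secondary outcome and does not justify the size for the primary one.

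The cost is one re-run and one reworded paragraph. The correction does not itself call for a change in enrolment. If the intended inputs turn out to need a different n, the paragraph should say so.

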#### Sampling method and randomization

The researcher will initiate the process by obtaining ethical approvals from the Tehran University of Medical Sciences. Following this, they will secure the required legal documents and permits from the Medical Vice-Chancellor of Tabriz and Tehran Universities of Medical Sciences. If necessary, this will allow them to conduct sampling within hospitals, clinics, and facilities under the university's jurisdiction, including private properties.

Subsequently, the researcher will visit the gynecological clinics within these facilities. In collaboration with the department head and resident urogynecology specialist, they will identify individuals seeking GCS within this clinical setting.

The initial sampling will employ a convenience sampling method, with individuals expressing an interest in participating in the study. They were subsequently screened against the eligibility criteria. Eligible participants will then be categorized into two groups: the intervention group, which will receive education tailored to address genital area needs and concerns, and the control group, which will receive sexual health and reproductive education.

An independent individual not involved in the research will generate an allocation sequence using a computer program (randomizer) to allocate participants. The allocation process will be concealed by writing the type of training assigned to each participant on paper, which will then be sealed inside consecutively numbered opaque envelopes.

Following the entry of each eligible participant into the Study (after obtaining informed consent and collecting primary data), the envelopes will be opened sequentially, and the participant will be assigned to a group according to the order of entry into the study.

#### Participant recruitment and data collection

Upon identifying eligible participants, informed consent will be obtained, and the participants will proceed to complete the study questionnaires. Given that many genital cosmetic surgeries are conducted in hospitals and private clinics, the researcher will initiate sampling in these facilities after making the necessary arrangements in case access to potential participants in these settings is limited.

Following the intervention sessions in both the intervention and control groups, changes in the participants' awareness and attitudes regarding the decision to undergo cosmetic surgeries will be reassessed.

Regarding blinding, this study will employ one-way blinding. Due to the nature of the intervention, it is not feasible to blind the researcher or the participant. However, to ensure the blinding of the outcome assessor, the questionnaires will be administered and completed by the researcher's assistant.

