##### Primary outcomes

Intention to undergo or actual performance of genital cosmetic surgeries.

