#### Data collection process

Attitudes toward GCS: Participants' attitudes and opinions regarding GCS will be assessed using items developed during the qualitative phase of the study. These items will provide insights into participant's perceptions and concerns regarding these procedures.

In the quantitative phase of this study, we will employ a researcher-developed questionnaire, which has been meticulously designed and validated based on the findings from the qualitative phase. After securing informed consent, we will initiate data collection using this questionnaire. The initial data will encompass participants' demographic, sexual, and reproductive characteristics. Additionally, participants will be asked to complete the standard FSFI [19] to assess sexual function and genital self-image to evaluate by using the FGSIS [20].The FSFI is comprised of 19 items categorized into six sub-domains, each assigned a specific weight or coefficient. These sub-domains include sexual desire (2 items with a coefficient of 0.6), sexual arousal and orgasm (4 items with a coefficient of 0.3 each), orgasm and satisfaction (3 items with a coefficient of 0.4 each), and pain (2 items with a coefficient of 4/0). Participants will respond on a Likert scale ranging from 0 to 5. A score of zero signifies no sexual activity within the past 4 weeks. After applying the coefficients, the overall score will fall between 2 and 36, with a lower score (FSFI ≤ 26) indicating less favorable sexual performance [21].FGSI is a 7-item patient-reported assessment tool designed to evaluate one's genital self-image. Participants rate each FGSIS item using a 4-point Likert-type scale, with options ranging from 1 (strongly disagree) to 4 (strongly agree). The individual item scores are summed to calculate the total score, falling within a range of 7–28 points. Higher total scores on the FGSIS signify a more positive genital self-image [22].The demographic profile questionnaire will encompass inquiries related to socio-economic status, including age, marital status, educational background, occupation, income, number of pregnancies and deliveries, and any history of illness or medication usage.

Furthermore, data collection will include an assessment of participants' attitudes toward undergoing GCS. The questions for this assessment were formulated during the qualitative phase of the study.

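### Assessor blinding cannot hold for the self-reported outcomes, and the article contradicts itself on who completes the questionnaires

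*Protocol article*

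**What the plan says.** The blinding statement is in the Phase III section Participant recruitment and data collection. It opens "Regarding blinding, this study will employ one-way blinding", concedes that "it is not feasible to blind the researcher or the participant", and then gives the means of protecting assessment: "to ensure the blinding of the outcome assessor, the questionnaires will be administered and completed by" the researcher's assistant.

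The same section, describing what follows consent, says "the participants will proceed to complete the study questionnaires". The Phase III section Data collection process also has participants complete the FSFI and rate each FGSIS item, and it states that "FGSI is a 7-item patient-reported assessment tool". Attitudes are taken from the participants' own views.

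The primary outcome is "Intention to undergo or actual performance of genital cosmetic surgeries". The secondary outcomes are the FSFI and the FGSIS before and after the intervention. Both arms are taught: the intervention arm receives education tailored to genital needs and concerns, set against "the control group, which will receive sexual health and reproductive education".

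**The concern.** Blinding an outcome assessor protects a judgement made by someone other than the participant. Here the judgement on most outcomes is the participant's, and the article says she cannot be blinded. Changing who hands out or fills in the form leaves that unaltered, so a report of blinded assessment would credit these outcomes with a protection they lack.

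The wording also matters in practice. If the assistant really completes the forms, women give answers on sexual function, genital self-image and the wish for surgery to a member of the study team, after teaching from that study on the same decision. This invites socially desirable answers, and stated intention is part of the primary outcome.

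**Working it through.** No figure in the article depends on the blinding claim, so the check is mainly a comparison of statements.

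**1. Who supplies each outcome?**

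| Outcome | Source in the article | Can a separate assessor make it blind? |
|---|---|---|
| Intention to have surgery (primary) | The woman's own statement | No |
| Surgery performed (primary) | An event; source not stated | Yes, if verified independently |
| FSFI (secondary) | Participant asked to complete it | No |
| FGSIS (secondary) | Patient-reported, participant rates each item | No |
| Attitudes to surgery | Participant's own opinions | No |

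**2. Is the assistant blind?** The article says who handles the forms, not that this person is unaware of allocation. Using someone other than the researcher does not by itself establish blinding.

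**3. Who completes the forms?** The sentence on what follows consent says the participants. The FSFI and FGSIS descriptions say the same. The blinding sentence says the assistant. These cannot all be followed as written.

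**4. When would the conflict bite?** Sampling method and randomization has the envelope opened after consent and collection of the primary data, which I read as baseline. At baseline nobody knows the arm, so the blinding sentence can only matter afterwards. One natural reading is therefore self-completion at baseline and assistant completion at follow-up. That change of mode would be mixed into any before-after comparison within an arm (paired t-tests are listed under Analysis approach). It would affect the comparison between arms only if women in the two arms respond to the change differently.

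**5. What could a differential shift do?** This is an illustration on an assumption that is not in the documents. Suppose there is no true effect on a scale score, but reporting differs between arms by b standard deviations. With the article's 15 per group before dropout and a two-sided 5% t-test, the rejection probability is P(|T| > 2.048), where T is noncentral t with 2 × 15 − 2 = 28 degrees of freedom and noncentrality b√(15/2).

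- b = 0.2: noncentrality 0.548, rejection about 8%
- b = 0.3: noncentrality 0.822, rejection about 12%
- b = 0.5: noncentrality 1.369, rejection about 26%

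The nominal rate is 5%. These figures concern a continuous scale, so the secondary outcomes. They show sensitivity and do not estimate the bias in this trial.

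**The case against.** The article is open about its limits: it claims one-way blinding only and says outright that researcher and participant know the arm. An administrator other than the unblinded researcher is a sensible step. If that person does not know the allocation, leading prompts and biased recording are less likely. How the assistant is kept unaware is an operational detail that a condensed article may leave to the full protocol. The control arm is an active education programme, which may reduce any difference in expectation between arms, and only a difference between arms biases the comparison. All of this stands. None of it makes the woman's own answers blinded, and none of it settles who completes the forms.

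A reader might go further in four ways that the documents do not support:

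- That every outcome is self-reported. The primary outcome includes surgery performed, which can be checked even though the article names no source for it.
- That there is no protection at all. It is limited and undocumented, which is a weaker statement.
- That the trial has given up the chance to keep women unaware of which programme is under test. This depends on consent and session wording that is not shown.
- That the bias can be stated as a share of the planned difference in genital self-image. Any shift would be assumed, the scale is a secondary outcome, and the planning mean of 29.09 lies above the stated FGSIS maximum of 28 if it refers to that scale.

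**Conclusion.** The point holds as a limit on the blinding claim and as an internal contradiction. Assessor blinding cannot apply to intention, attitudes, the FSFI or the FGSIS. It could apply to surgery performed, if that is verified by someone unaware of allocation. The instruction that the assistant completes the questionnaires conflicts with three other statements in the article: the sentence on what follows consent, the FSFI description and the FGSIS description.

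The size of any resulting bias is unknown, and the documents give nothing to estimate it from. The expected direction, towards the message of the tailored programme, rests on the assumption that women in that arm are more inclined to give the answer they think is wanted. The mode-change concern rests on one reading of ambiguous text. The correction is worth making because part of the primary outcome is exposed and the remedy is nearly free.

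**What to change.** - **Blinding statement.** Say that intention, attitudes, FSFI and FGSIS are self-reported by unblinded participants. Limit any claim of blinded assessment to outcomes that can be verified independently, such as surgery performed.
- **Who completes the forms.** Reconcile Participant recruitment and data collection with Data collection process, so that women complete the questionnaires themselves, privately and on coded forms, in the same way before and after the intervention. An assistant kept unaware of allocation gives help with reading only where needed, since the trial admits women with minimal literacy.
- **Description of the arms.** As both arms receive education, describe the two programmes neutrally to participants where feasible.

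The cost is a few sentences of procedure and participant-facing text. Self-completion may leave a few more items missing.

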#### Study variables and outcomes

After the trial phase, the following variables and outcomes will be examined:

Independent Variables (Educational Interventions): These are the interventions designed and implemented as part of the study.

Dependent Variable: The primary dependent variable is the decision to undergo or refrain from GCS, which will be assessed at the end of the trial phase.

##### Primary outcomes

Intention to undergo or actual performance of genital cosmetic surgeries.

##### Secondary outcomes.

Women's Female Sexual Function Index (FSFI) before and after the intervention.Women's Female Genital Self-Image Scale (FGSIS) before and after the intervention

#### Data collection process

Attitudes toward GCS: Participants' attitudes and opinions regarding GCS will be assessed using items developed during the qualitative phase of the study. These items will provide insights into participant's perceptions and concerns regarding these procedures.

In the quantitative phase of this study, we will employ a researcher-developed questionnaire, which has been meticulously designed and validated based on the findings from the qualitative phase. After securing informed consent, we will initiate data collection using this questionnaire. The initial data will encompass participants' demographic, sexual, and reproductive characteristics. Additionally, participants will be asked to complete the standard FSFI [19] to assess sexual function and genital self-image to evaluate by using the FGSIS [20].The FSFI is comprised of 19 items categorized into six sub-domains, each assigned a specific weight or coefficient. These sub-domains include sexual desire (2 items with a coefficient of 0.6), sexual arousal and orgasm (4 items with a coefficient of 0.3 each), orgasm and satisfaction (3 items with a coefficient of 0.4 each), and pain (2 items with a coefficient of 4/0). Participants will respond on a Likert scale ranging from 0 to 5. A score of zero signifies no sexual activity within the past 4 weeks. After applying the coefficients, the overall score will fall between 2 and 36, with a lower score (FSFI ≤ 26) indicating less favorable sexual performance [21].FGSI is a 7-item patient-reported assessment tool designed to evaluate one's genital self-image. Participants rate each FGSIS item using a 4-point Likert-type scale, with options ranging from 1 (strongly disagree) to 4 (strongly agree). The individual item scores are summed to calculate the total score, falling within a range of 7–28 points. Higher total scores on the FGSIS signify a more positive genital self-image [22].The demographic profile questionnaire will encompass inquiries related to socio-economic status, including age, marital status, educational background, occupation, income, number of pregnancies and deliveries, and any history of illness or medication usage.

Furthermore, data collection will include an assessment of participants' attitudes toward undergoing GCS. The questions for this assessment were formulated during the qualitative phase of the study.

